### Data analysis

Data will be analyzed on an intention-to-treat and a per protocol basis. Data will be presented as means with standard deviations and Student’s *t* test will be used to compare differences in proportions between the groups. Significance will be set at the 5% level. No interim evaluation of the data is planned.

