### Outcome measures

The outcome measures used to compare differences between the study arms will include:

Primary

PRAM score at Day 4

Secondary

Relapse rate – a relapse will be defined as any visit to a healthcare provider, for example, General Practitioner, ED, as a result of asthma symptoms within 14 days of study enrolment

Number of salbutamol therapies given following enrolment

Side effects, in particular, vomiting

Compliance with medication, assessed by interview and the return of study packs

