### Statistical considerations

The aim of this study is to demonstrate that a single dose of dexamethasone is clinically non-inferior to a three-day course of prednisolone.

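### The only named test, Student's t, is assigned to proportions, and no analysis is tied to the 1-point non-inferiority margin on mean Day 4 PRAM

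*Protocol article*

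**What the plan says.** The analysis method is stated in one sentence of the Data analysis section. It begins "Data will be presented as means with standard deviations and Student’s" and ends by saying that this "test will be used to compare differences in proportions between the groups". The section adds intention-to-treat and per-protocol analyses, a 5% significance level and no interim look. It names no confidence interval and does not mention the margin. The section on bias and confounding adds adjustment if there is imbalance, without naming a method.

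The trial's aim, under Statistical considerations, is to show that a single dose is "clinically non-inferior to a three-day course of prednisolone". Outcome measures lists one primary outcome, "PRAM score at Day 4". The Sample size and power section sets the non-inferiority criterion on the average PRAM score (dexamethasone no more than one point higher), yet pairs it with a null hypothesis of equal population means.

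The secondary outcomes are of several types. Relapse is yes/no ("a relapse will be defined as any visit to a healthcare provider", for asthma symptoms within 14 days), and vomiting is naturally yes/no ("Side effects, in particular, vomiting"). The salbutamol outcome is a count ("Number of salbutamol therapies given following enrolment"). Compliance has no stated scale ("Compliance with medication, assessed by interview and the return of study packs").

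**The concern.** A t test compares means. As written, the sentence gives the one named test to proportions and leaves the mean PRAM comparison, on which the trial is designed, without a method. It also contradicts its own opening words and the sample size section.

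The primary conclusion is what is at stake. A non-inferiority claim requires the confidence limit for the difference in means to lie inside the margin. A 5% test of equality answers another question, and a non-significant result from it does not establish non-inferiority. Nothing in the Data analysis section stops such a result being reported as showing that the treatments are alike. For the yes/no outcomes, the sentence offers means, SDs and a t test where counts, percentages and an interval for the risk difference are needed.

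**Working it through.** **1. Which contrast was the trial designed on?** Inputs from Sample size and power: margin 1 point, SD 2.23 (the ED-discharge value; the text does not say which SD was used), power 0.90, alpha 0.05 (sidedness not stated).

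n per group = 2 × (1.960 + 1.282)² × 2.23² / 1² = 104.5, rounded up to 105.

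This matches the stated 105, for a two-sided 5% test or equally for a one-sided 2.5% non-inferiority test. Adding 10% gives 105 × 1.1 = 115.5, so 116 per group and 232 in total, as stated. (Dividing by 0.9 would give 117 per group and 234.) The alternatives do not reproduce it: one-sided 5% with SD 2.23 gives 86 per group, and SD 1.5 gives 48 (two-sided) or 39 (one-sided). The design is therefore a comparison of two means.

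**2. What can a 5% significance test miss?** With 105 per group and SD 2.23:

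- SE = 2.23 × √(2/105) = 0.308
- 95% half-width = 1.971 × 0.308 = 0.607 (t, 208 df)
- Observed +0.5: t = 0.5/0.308 = 1.62, p = 0.11; 95% CI 0.5 ± 0.607 = -0.11 to 1.11

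This result is not significant, but the interval crosses 1.0. More generally, the difference is non-significant up to +0.607, while the upper limit stays below 1.0 only up to 1 - 0.607 = +0.393. Any observed excess between about 0.39 and 0.61 points is non-significant and still fails non-inferiority. A larger SD or heavier loss to follow-up widens that band.

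**3. Does the t test distort the binary outcomes?** Two binomials with 105 per arm and equal event rates were enumerated exactly. Chance of p < 0.05:

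| Event rate | t test on 0/1 data | Uncorrected chi-square | Fisher's exact |
|---|---|---|---|
| 1% | 1.51% | 1.51% | 0.05% |
| 3% | 4.45% | 4.45% | 1.23% |
| 7% | 5.05% | 5.05% | 2.69% |

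The t test and chi-square did not disagree at the 5% level in any scenario tried. The choice between those two and Fisher's test matters when events are few: 4 versus 0 gives p = 0.044 (t), 0.043 (chi-square) and 0.121 (Fisher); 5 versus 0 gives 0.024, 0.024 and 0.060.

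**4. Does it distort the intervals?** For 4/105 versus 0/105 the risk difference is 3.8 percentage points. The t-based interval uses pooled variance 4 × (1 - 0.0381)/208 = 0.0185 and SE √(0.0185 × 2/105) = 0.0188, which gives 0.1 to 7.5 points. The Newcombe score interval, built from Wilson limits of 1.49% to 9.39% and 0% to 3.53%, is:

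- lower: 3.81 - √((3.81 - 1.49)² + 3.53²) = -0.4
- upper: 3.81 + (9.39 - 3.81) = 9.4

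The t-based interval excludes zero and stops nearly two points lower at the top. Rates this low are plausible: in Table 1, the 628-patient oral dexamethasone trial reports exclusions for vomiting of 3% versus 0.3%.

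**The case against.** The strongest reply is that one word is wrong. The sentence opens with means and SDs, and the sample size section assumes normality and compares means, so proportions is very likely a slip for means. On that reading the primary test is stated, and the article does give the endpoint, margin, alpha and analysis sets. This largely stands, and it would overstate the matter to say that the primary comparison has no decision criterion. But correcting the word leaves a significance test that is not linked to the margin, and it leaves relapse and vomiting under means and a t test.

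A reader might infer that the t test would give badly wrong p values for relapse, vomiting and compliance. The documents do not support that. The t test tracks the uncorrected chi-square; its low rejection rate at 1% comes from sparse data; and Fisher's test is further from nominal at every rate in the table. Nor are all these outcomes known to be rare and binary. The compliance scale is undefined, the Background cites only 64% adherence in one study, and the 89-patient trial in Table 1 reports vomiting of 18% versus 10%. At a 7% relapse rate the 95% half-width is 1.96 × √(2 × 0.07 × 0.93/105) = 6.9 percentage points, but that comes from the sample size, not from the choice of test. It supports showing an interval and nothing more.

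The model for the salbutamol count and its summary statistics are commonly left to an analysis plan, which is not shown, so their absence is no finding. An unseen plan could add detail, but it would not make the published sentence correct.

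**Conclusion.** The point holds in a limited form. The sentence assigns its test to the wrong type of outcome, against its own opening and against a sample size that reproduces as a two-means calculation. The main consequence is for the primary conclusion: under the design assumptions (105 evaluable per group, SD 2.23), an observed dexamethasone excess of roughly 0.39 to 0.61 points would be non-significant without showing non-inferiority. For binary outcomes the effect on p values is small, and the gain from correction is sound intervals when events are rare. The numbers assume the discharge SD applies at Day 4 and two-sided 95% intervals; the article states neither.

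**What to change.** Replace the sentence with two statements.

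- **Primary:** the difference in mean Day 4 PRAM (dexamethasone minus prednisolone), t-based, with a two-sided 95% CI. Non-inferiority is concluded if the upper limit is below 1.0 in both the intention-to-treat and per-protocol sets. The null hypothesis in Sample size and power should be reworded to match (a true difference of 1 point or more).
- **Binary outcomes (relapse, vomiting):** numbers and percentages by group, with a risk difference, a 95% score interval, and a chi-square test, or an exact test when events are sparse by a rule set in advance.

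The cost is one reworded paragraph and standard software. The sample size stands: 105 per group gives 89.9% power at two-sided 5% by the noncentral t. Trial Status reports recruitment complete in July 2012 and analysis starting in September 2012, so the change should be dated before the data are analysed by group.

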### Bias and confounding variables

In terms of selection bias, we feel that this study targets a representative patient population to whom this research ultimately may be clinically applicable. Every effort will be made to ensure that recruitment of participants occurs over all 24-hour periods and at weekends by having patients recruited by the ED physician treating the patient.

We anticipate that the randomized controlled design of this study will minimize the effect of confounding variables on our analysis. However, all potential confounders (that is, age, asthma severity, concomitant medications) will be measured during data collection and they will be adjusted for during the analysis should there be any imbalance. Also, every effort will be made to ensure that the physician who is assessing the primary outcome is blinded to the treatment allocation.

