**Methods/design:**

This is a randomized, non-inferiority, open-label clinical trial. After informed consent with or without assent, patients will be randomized to either oral dexamethasone 0.3 mg/kg stat or prednisolone 1 mg/kg/day for three days. The primary outcome measure is the comparison between the Pediatric Respiratory Assessment Measure (PRAM) across both groups on Day 4. The PRAM score, a validated, responsive and reliable tool to determine asthma severity in children aged 2 to 16 years, will be performed by a clinician blinded to treatment allocation. Secondary outcomes include relapse, hospital admission and requirement for further steroid therapy. Data will be analyzed on an intention-to-treat and a per protocol basis. With a sample size of 232 subjects (105 in each group with an estimated 10% loss to follow-up), we will be able to reject the null hypothesis - that the population means of the experimental and control groups are equal with a probability (power) of 0.9. The Type I error probability associated with this test (of the null hypothesis) is 0.05.

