### Study procedure

#### General description

Before the start of the study, the research team will conduct training sessions for all ED nurses and physicians to explain roles and responsibilities and all aspects of the study. Training sessions on the PRAM score have also taken place, and this score has been used in the assessment of all asthma exacerbations (over the age of 2) presenting to the ED from April 2011 onwards.

Eligible participants will be identified at triage or during clinical consultation by the ED clinician. They and their parents/guardians will be provided with written and verbal information about the study. All patients in the study will be recruited by a member of the research team or an ED clinician.

After eligibility for inclusion in the study is confirmed, the research trial and procedures involved will also be explained to the patient in age-appropriate language. In all cases, where appropriate, informed assent will be obtained from the patient. This may not be possible in younger patients and in patients who are too unwell (for example, short of breath) to actively participate in the consent process. If the patient recovers sufficiently, we will go through the assent process with them at a later stage. In all cases without exception, informed consent will be obtained from the parent/legal guardian. If a patient refuses assent they will not be included in the study, even if a parent/legal guardian gives consent.

The informed consent process will be documented in the medical notes (including the date/time of consent and the provision of information to the patient/parent(s)/guardian). Once the patient is consented, randomization will occur.

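### Adjustment of the Day 4 PRAM comparison is triggered by undefined imbalance, so the data choose the analysis; a fixed model on pre-randomization covariates would be clearer and more powerful

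*Protocol article*

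**What the plan says.** Under Bias and confounding variables, the protocol article states that "all potential confounders (that is, age, asthma severity, concomitant medications) will be measured during data collection" and that "they will be adjusted for during the analysis should there be any imbalance". It does not say how imbalance is judged, when the covariates are measured, what model is used, or whether an adjusted result replaces or supports the unadjusted one.

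Under Data analysis the only method named is Student's t, in the words "test will be used to compare differences in proportions between the groups". For a mean score this has to be read as a comparison of means. The same section adds: "Data will be analyzed on an intention-to-treat and a per protocol basis".

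The primary outcome is "PRAM score at Day 4". Sample size and power treats dexamethasone as non-inferior if its mean is no more than one point above that of prednisolone, and sizes the trial without any covariate term.

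Two kinds of medication given after enrolment are themselves outcomes. Outcome measures lists "Number of salbutamol therapies given following enrolment", and the abstract says "Secondary outcomes include relapse, hospital admission and requirement for further steroid therapy".

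On the baseline score, General description says of PRAM that "this score has been used in the assessment of all asthma exacerbations" in children over 2 since April 2011. Regulatory approval followed in June 2011.

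**The concern.** Randomized arms always differ a little, so a trigger of any imbalance, with no threshold, can justify either adjusting or not adjusting. The choice is then made with the data in hand, in an open-label trial. Two estimates of the same difference become available in each analysis set, and the text does not say which is held against the margin. A non-inferiority conclusion that holds under one and fails under the other could not be settled from the protocol.

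The covariate list raises a second question. Age is fixed before randomization. Concomitant medications need not be: the term could cover salbutamol or further steroids given afterwards, which may respond to the assigned treatment. Conditioning on them would change what is being estimated.

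Third, adjustment for a baseline score that predicts the outcome works best when it is planned. Making it conditional on imbalance gives up most of that benefit.

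**Working it through.** **Inputs.** From Sample size and power: margin 1 point, SD 2.23 (PRAM at ED discharge; no Day 4 SD is given), power 0.90, type I error 0.05 with sidedness not stated, 105 per group, 232 in total with 10% loss. Assumed, because the article does not give them: the correlation r between covariates and Day 4 PRAM, and a threshold for imbalance.

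**1. The plan's own figure.**
n per group = 2 × (1.960 + 1.282)² × 2.23² / 1² = 104.5, so 105. This needs one-sided 0.025 (two-sided 0.05); one-sided 0.05 gives 86. Loss to follow-up: 210 × 1.10 = 231, and 2 × 116 = 232. The stated size reproduces, as an unadjusted calculation.

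**2. How often chance alone triggers adjustment.** With three independent covariates each tested at level a, P(at least one flagged) = 1 − (1 − a)³:
- a = 0.05: 14.3%
- a = 0.10: 27.1%
- a = 0.20: 48.8%

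So an unstated threshold moves the share of trials analysed with adjustment from about one in seven to about one in two.

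**3. Operating characteristics of the rule.** Simulation with 105 per arm, SD 2.23, three independent normal covariates with joint correlation r with the outcome, imbalance flagged at 10%, and 20,000 runs per scenario. Non-inferiority is declared if the upper 95% limit is below 1. Under the mechanical rule only flagged covariates enter; the planned model always contains all three.

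| | r = 0.3 | r = 0.5 | r = 0.7 |
|---|---|---|---|
| Type I error, mechanical rule | 0.024 | 0.020 | 0.016 |
| Type I error, planned adjustment | 0.025 | 0.023 | 0.025 |
| Type I error, better of unadjusted and fully adjusted | 0.032 | 0.035 | 0.042 |
| Power, mechanical rule | 0.904 | 0.914 | 0.929 |
| Power, planned adjustment | 0.920 | 0.960 | 0.995 |

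The simulation error at 0.025 is √(0.025 × 0.975 / 20,000) = 0.0011. The mechanical rule is conservative because the trials left unadjusted are the better balanced ones, and their estimates vary less than the unadjusted standard error assumes.

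**4. Gain from planned adjustment for triage PRAM.** Residual SD = 2.23 × √(1 − r²); power by noncentral t at 105 per arm:

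| Assumed r | Variance reduction r² | Residual SD | Power |
|---|---|---|---|
| 0 | 0% | 2.23 | 0.899 |
| 0.3 | 9% | 2.127 | 0.924 |
| 0.4 | 16% | 2.044 | 0.942 |
| 0.5 | 25% | 1.931 | 0.962 |

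**5. If post-randomization medication were adjusted for.** SE = 2.23 × √(2/105) = 0.308. Suppose the true difference equals the margin and adjustment moves the estimate by m points towards zero, with the SE held fixed. P(declare non-inferiority) = Φ(m/0.308 − 1.96):
- m = 0.1: 0.051
- m = 0.2: 0.095
- m = −0.1 (estimate enlarged): Φ(−2.285) = 0.011

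The shifts are assumed. A worse arm that uses more salbutamol could move the estimate in either direction: downwards if use mainly marks poor response, upwards if use itself lowers the Day 4 score and so masks a difference.

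**The case against.** The strongest reply is that the sentence is a general safeguard and its details belong to an analysis plan not shown here. The article names one test and sizes the trial on it, so an unadjusted primary analysis with an adjusted one in support fits the text. That is a fair reading, but the text does not settle on it. What the article does state is an imbalance-triggered rule, and an analysis plan that followed it would carry the same weakness.

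A reader might infer that the rule inflates the type I error. The documents do not support that. Followed mechanically, it errs on the safe side and keeps power just above the planned 0.90. Inflation needs a free choice of the better result, which the article does not propose and merely fails to exclude.

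A reader might also infer that adjusting for concomitant medications would remove part of the effect and favour non-inferiority. That goes too far as well. Listed beside age and asthma severity, in a passage about what randomization balances, the term most naturally means medication at presentation. Salbutamol after enrolment is listed separately as an outcome, and nothing says it enters a model. Even on the wider reading, the direction of bias is not fixed. What remains is an ambiguity to close.

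Nor is the baseline score simply ignored, since asthma severity is on the list. That triage PRAM is held for every trial child is a reasonable inference from its routine use, but it is not stated.

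**Conclusion.** The point holds as a badly fixed rule with a better alternative that costs almost nothing. The article lets observed imbalance, undefined, decide whether the Day 4 comparison is adjusted, and leaves open which estimate meets the margin. The cost of following the rule literally is lost power relative to planned adjustment: about 2 percentage points at joint r = 0.3, 5 at 0.5 and 7 at 0.7. The cost of leaving the choice open is a one-sided error of about 0.03 to 0.04 in place of 0.025, if the favourable result is taken. Both rest on assumed correlations and a 10% flag. The medication question is conditional: it matters only if use after randomization is included, and then the adjusted estimate is not the treatment effect, with bias of unknown sign. The 105 per group is correctly derived, and the gain to about 92% to 96% power is a benefit on offer, not a correction of a shortfall.

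**What to change.** Replace the imbalance rule with a statement on these lines: the primary analysis is an ANCOVA of Day 4 PRAM on treatment, triage PRAM and age, fitted whatever the observed balance; only variables measured before randomization enter the model; the 95% confidence interval for the adjusted difference (dexamethasone minus prednisolone) is compared with 1.0; the unadjusted difference is a supporting analysis. If medication use is kept as a covariate in a further sensitivity analysis, restrict it to use before randomization.

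The cost is one sentence and two degrees of freedom for covariates, with no extra patients. Age is already to be collected; that triage PRAM is on file for each child should be confirmed. Trial Status puts the start of analysis in September 2012, after recruitment closed in July 2012, so on the article's dates the model could still be fixed before any comparison of the arms.

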### Safety reporting

All adverse events (AEs) that occur during the study period observed by one of the clinical staff, or reported by the patient or parent/guardian spontaneously, or in response to a direct question, will be noted on the appropriate form. These forms are de-identified. The following procedures will take place depending on the type of event that has occurred.

### Adverse event (AE)

Each AE will be recorded by a member of the research team on an AE Form. AEs will be classified on the form in terms of their severity, association with the study drug, expectedness and seriousness. They will be recorded on an AE Log. The AEs will be reported to the Sponsor and the institutional HREC on a yearly basis as part of an annual safety report and at the end of the trial.

### Serious adverse event (SAE)

Each SAE will be recorded by a member of the research team on an SAE Form. SAEs will be classified on the form in terms of their severity, relatedness to the study drug and expectedness. They will be recorded on a SAE Log. All SAEs will be reported on the SAE form within 24 hours to the Sponsor and the Research Ethics Committee. The research team will ensure that follow-up information and a detailed written report are provided when available.

### Suspected unexpected serious adverse drug reaction (SUSAR)

Each SUSAR will also require expedited reporting to the Sponsor. This will occur as soon as possible, but no later than 24 hours after a member of the research team has first knowledge of the minimum criteria for expedited reporting. In each case, relevant follow-up information should be sought and a detailed, written report completed as soon as possible. It is the Sponsor’s responsibility to ensure that all relevant and available information is forwarded to the Competent Authority (Irish Medicines Board) and the appropriate health ethics committee (HREC, OLCHC). For fatal or life-threatening events this will be done as soon as possible and not later than seven days after the Sponsor becomes aware of the event. Additional relevant information will be sent within eight days of the first report. This will be sent no later than an additional 15 calendar days. For AEs that are not fatal or life-threatening, the Sponsor will ensure that a SUSAR is reported as soon as possible and in any event not later than 15 days after the Sponsor is first aware of the event.

The parents of participants will be provided with 24-hour contact details of a study representative if they have concerns about any component of the study or their child’s condition. We will also report to the hospital Risk Management Team and the Drugs Advisory Committee of the study site.

